### Composition of placebo

**Table Taba:** 

Inactive placebo based on cellulose with a non-therapeutic input of cocoa powder (for colour matching).	

### Outcome measures and data capture

All data will be captured electronically via the secure electronic data capture platform Castor EDC [13]. Signed consent forms will be digitally captured and securely stored in Castor EDC.

Participants will not be required to physically attend any of the study visits for the trial, with the exception of two blood tests at certified pathology collection centre. The total study duration is 20 weeks: 4 weeks prior to trial entry to perform baseline pain screening diary, 12 weeks of active treatment and 4 weeks of follow-up. Six study visits/checkpoints will be required: (1) screening (confirm eligibility), (2) baseline (blood collection followed by dispensing medication), (3) week 6 phone call (check adverse events, compliance and medication use), (4) midpoint (week 12; check adverse events, compliance, medication use and dispense medication), (5) end of treatment (week 16; check adverse events, compliance and medication use and blood collection) and (6) post-treatment follow-up (week 20; check adverse events and collect pain diary scores of 1 month).

All data will be securely held on the study team database, accessible only by authorised investigators for the purposes of monitoring. The final dataset will be accessible by the coordinating investigators and each locality will retain on-site access to digital copies of source documentations with paper copies stored in secure archives.

Any changes to the study protocol are provided to the Human Research Ethics Committee as per protocol, trial registries will be updated. A copy of the consent form is included as Supplementary File 1.

Clinical assessments and patient surveys will be completed using Castor clinical trials management software. All the pre-specified outcome measures are outlined in Table 3:

**Table 3 Tab3:** Outcome measures

**Primary outcome measure:**	
To evaluate the efficacy of Gynoclear™ by change in endometriosis-related pain based on the Endometriosis pain daily diary v3 (EPDD) scores.	
**Secondary outcome measures:**	
To assess the change in health-related quality of life via the Endometriosis Health Profile (EHP-30), SF-12 and EQ. 5D scores.	
To assess any changes in use of pharmaceutical analgesics via the EPDD	
To assess any changes in dyspareunia (painful sexual intercourse) via the EPDD.	
To assess any changes in fatigue via the EPDD and fatigue severity scale (FSS)	
To assess any changes in restrictions to activities of daily living via the EPDD.	
To monitor the frequency and severity of adverse events during intervention period.	
To determine the cost-effectiveness of using Gynoclear™.	
To explore participant satisfaction with the intervention.	

#### EPDD

Participants will have access to the EPDD v3 [12] via an online web form. After focus groups with over 40 women with endometriosis, they identified that their top three symptom priorities were pelvic pain, fatigue and dyspareunia. The EPDD v3 already tracks pelvic pain and dyspareunia so modifications were made to include a daily fatigue score (0–10) in the same format.

#### Participant expectation and satisfaction questionnaires

At trial entry, participants will be asked about their current symptoms, and what expectations they have regarding changes of pain and other symptoms during the trial.

At the trial exit, participants will be asked to indicate which group they thought they were in, rate their satisfaction with the treatment given, what (if any) symptoms changed and what impact this had on them. Additional open-ended questions will explore acceptability including their experiences participating in the trial, likelihood of recommendation of the intervention to family and friends, interest in using the intervention again for pelvic pain symptoms, and feedback on the trial design and outcomes collected.

#### Health-related quality of life questionnaires

The Endometriosis Health Profile-30 (EHP-30) is an endometriosis specific health-related quality of life measure [14]. It covers pain, control and powerlessness, social support, emotional well-being and self-image. These 30 questions provide the core of the EHP-30. The EHP also includes optional secondary modules that may not be appropriate to all participants. If participants are currently working, they will be asked to fill in the ‘Work’ module, if they are currently in a sexual relationship, they will be asked to fill in the ‘Sexual relationship’ module. All measures have a 1 month recall and will be taken twice online; at baseline and at the end of the 4-week follow-up period.

The EQ-5D [15] and SF12 [16] are validated health-related outcome measures and provide the necessary data for economic analysis and have been recently used in our economic analysis of the impact of endometriosis in Australia [17]. The EQ-5D is administered via Castor EDC and the SF-12 will be administered via paper-based methods due to cost, at baseline and at the end of the 4-week follow-up period.

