#### Fatigue severity scale (FSS)

The fatigue severity scale is a nine-item, seven-point questionnaire used to determine the impact of fatigue when performing daily activities [18]. This will be used as an adjunct to the numerical ratings given for daily fatigue, to provide a measure of the real-world impact of fatigue. This tool uses a seven-day recall. This will be administered online at baseline and at the end of the intervention.

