### Analysis plan

All data is captured via Castor EDC digitally, there are no paper instruments used in this trial. Data will be exported from Castor EDC into SPSS v24 (or greater). Prior to analysis, data will be cleaned by examining frequencies, means, medians, and ranges to identify logical errors. Instruments will be coded according to their respective scoring instructions. Unless specified by the instrument, missing items will be imputed based on averaging values within the instrument for a given individual, if no more than 15% of items are missing. Otherwise, that instrument will be set to missing for the individual.

Baseline demographics will be reported using descriptive statistics. Daily pain scores (as measured by the EPDD) will be converted into a single pain score at five time points, baseline, month 1, month 2, trial exit/end of intervention and follow-up. This single pain score will be achieved by taking the mean of the daily pain scores for the previous 4 weeks. Both a per-protocol and intention to treat analysis will be undertaken for the primary outcome of changes in pain scores. The same process of generating a single score will be used for the following outcomes: pain interference with activities of daily living (0–10), use of analgesics (number of days per month needing additional medication), severity of fatigue (0–10) and severity of dyspareunia (0–10). All scores will be analysed using repeated measures at baseline, month 1, month 2, trial exit and follow-up via a longitudinal linear mixed model analysis of variance with time and group as fixed effects and subject as a random effect.

Secondary outcomes of changes in EHP-30 scores, SF-12 scores and EQ-5D scores will be analysed using analysis of variance between baseline and one-month follow-up. FSS scores will be analysed using paired analysis of variance between baseline and the end of the intervention. Baseline values with be used as covariates in the analysis.

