A cost-effectiveness (cost-utility) analysis will be conducted alongside the trial following international best practice [19]. This will assess the difference between trial arms in (i) costs—the cost of introducing modified GZFLW and the use of analgesic medications, measured using Medicare Benefits Scheme/Pharmaceutical Benefits Scheme, and (ii) effects—the difference in an economic measure of health-related quality of life, called the EQ-5D, which is used in estimating quality-adjusted life years. A cost-effectiveness analysis, combining i and ii, will then be conducted including subgroup analysis. Further, statistical uncertainty will be explored in a Probabilistic Sensitivity Analysis, health-related quality of life will be cross-validated using the SF12, and a Value of Information analysis will assess whether further research is required before making recommendations to mainstream modified GZFLW in routine practice.

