### Study timeline

The expected duration of the data collection phase of this study will be 12 months, with 14 time points where data is collected. The schedule of enrolment, interventions and assessments as per SPIRIT [20] is outlined in Table 4.

**Table 4 Tab4:** Timeline of treatment assessments and interventions

Procedure	Screening (week 0)	Baseline (week 4)	Phone call (week 6)	Midpoint (week 10)	End of treatment (week 16)	Post-treatment follow-up (week 20)
Informed consent	X					
Inclusion and exclusion	X					
Medical history	X					
Screening blood test: LFT and U&E		X				
Randomisation		X				
Treatment/placebo dispensed		X				
End of treatment blood test: LFT and U&E					X	
Concomitant medication collection		X	X	X	X	X
Participants electronically fill out Endometriosis Pain Daily Diary v3 Scores	X	X	X	X	X	X
Quality of life forms (SF-12, EQ-5D, EHP-30)		X				X
Fatigue severity scale (FSS)		X			X	
Participant expectation and satisfaction questionnaire		X			X	
Adverse events			X	X	X	X
Dispense/return study drug		X		X	X	

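### EHP-30, SF-12 and EQ-5D have no reading during or at the end of treatment: the only post-baseline reading comes four weeks after treatment stops

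*Protocol article*

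**What the plan says.** The section on outcome measures and data capture gives "12 weeks of active treatment and 4 weeks of follow-up" after a four-week screening diary, and places the "end of treatment (week 16; check adverse events, compliance and medication use and blood collection" contact accordingly.

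The section on health-related quality of life questionnaires states for the EHP-30: "All measures have a 1 month recall and will be taken twice online; at baseline and at the end of the 4-week follow-up period". For the EQ-5D the electronic system is used, and "the SF-12 will be administered via paper-based methods due to cost, at baseline and at the end of the 4-week follow-up period"; the sentence covers both instruments.

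Table 4 (Study timeline) agrees. The row "Quality of life forms (SF-12, EQ-5D, EHP-30") is marked at baseline (week 4) and post-treatment follow-up (week 20), and is blank at weeks 6, 10 and 16. The analysis plan agrees too: these scores are to be "analysed using analysis of variance between baseline and one-month follow-up".

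The economic part of the analysis plan takes as its effect measure "the difference in an economic measure of health-related quality of life, called the EQ-5D, which is used in estimating quality-adjusted life years". The SF-12 serves there as a cross-check.

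The fatigue severity scale (FSS) is timed differently: "This will be administered online at baseline and at the end of the intervention". Table 4 marks it, and the expectation and satisfaction questionnaire, at week 16.

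**The concern.** The stated aim covers efficacy on quality of life as well as pain. Pain is summarised at baseline, month 1, month 2, end of intervention and follow-up, so its course on and off treatment can be seen. The three quality-of-life instruments have one post-baseline reading, taken when nobody is on the product. A benefit present at week 16 and lost by week 20 would show in the pain results and not in EHP-30, SF-12 or EQ-5D, and the two sets of results would answer different questions.

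The economic analysis is more exposed. The cost of the product accrues over the treatment weeks, while utility is observed only before and after them. The SF-12 cross-check cannot reveal the gap, because it is taken at the same two points.

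The matter cannot be left to an analysis plan that is not shown. The article fixes the collection schedule, and no analysis can use a reading that was not taken.

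**Working it through.** **Timeline.** Inputs are from the section on outcome measures and data capture and from Table 4.

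- Screening 4 weeks + treatment 12 weeks = week 16, end of treatment.
- Week 16 + follow-up 4 weeks = week 20. This reproduces the stated total of 20 weeks and the Table 4 columns.
- EHP-30 recall at week 20, taking one month as four weeks: weeks 16 to 20. Overlap with treatment (weeks 4 to 16): none.
- Readings of EHP-30, SF-12 or EQ-5D after baseline and up to week 16: 0.

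The abstract gives a different treatment length from the Methods, and the midpoint is week 12 in the text but week 10 in Table 4. Those passages must be reconciled, but neither discrepancy moves the second quality-of-life reading out of the post-treatment month.

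**Effect on QALYs.** The documents give no utility difference, no onset or offset of benefit, and no QALY formula. What follows is therefore an illustration under stated assumptions. Let D be the between-arm utility difference at week 16 and f the fraction of it present at week 20, with no difference at week 4. Areas are trapezoids, divided by 52 weeks.

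- Readings at weeks 4 and 20: 0.5 × fD × 16/52 = 8fD/52.
- Readings at weeks 4, 16 and 20: (0.5 × D × 12 + 0.5 × (D + fD) × 4)/52 = (8 + 2f)D/52.
- Share recovered by two readings: 8f/(8 + 2f) = 4f/(4 + f).

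| f | two readings, D = 0.10 | three readings, D = 0.10 | share recovered |
|---|---|---|---|
| 0 | 0.0000 | 0.0154 | 0% |
| 0.25 | 0.0038 | 0.0163 | 24% |
| 0.5 | 0.0077 | 0.0173 | 44% |
| 0.75 | 0.0115 | 0.0183 | 63% |
| 1 | 0.0154 | 0.0192 | 80% |

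**Other shapes.**

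- Benefit builds linearly from week 4 to week 20. Week 16 is then 12/16 of the week-20 value, so f = 16/12 = 4/3, and 4f/(4 + f) = (16/3)/(16/3) = 1. There is no error. For f above 4/3, two readings overstate the gain.
- Full benefit by week 8, held to week 16, then linear to fD at week 20. The true gain is (2 + 8 + 2(1 + f))D/52 = (12 + 2f)D/52. Two readings recover 8f/(12 + 2f): 0%, 16%, 31%, 44% and 57% for the five values of f.
- Full benefit D from the first day. If it is lost as treatment ends, the true gain is 12D/52 = 0.231D; two readings give 0 and three give 8D/52 = 0.154D. If it is kept to week 20, the true gain is 16D/52 = 0.308D; two readings give 8D/52 = 0.154D and three give 10D/52 = 0.192D.

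A week-16 reading therefore narrows the gap but does not close it when onset is fast.

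**The case against.** The schedule is consistent across three places, so it is a design choice and not a slip, and stakeholder groups had input on outcome measures and trial duration. A reader might nevertheless infer three stronger things, none of which the documents support.

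- *That quality of life on treatment is never measured.* Pain, interference with daily activities, fatigue, dyspareunia and analgesic days come from the daily diary and are analysed at month 1, month 2 and end of intervention. The FSS is taken at week 16. The gap is confined to the three named instruments, though none of these other measures is named as a source of utilities.
- *That the week-20 result is not an effect of Gynoclear.* A randomised difference at week 20 is an effect of allocation: that of a 12-week course, one month after it ends. What can be said is that it is a different quantity from the effect on treatment, and that the article does not label it so.
- *That the QALY analysis leaves out the treatment weeks and must understate benefit.* A straight line from week 4 to week 20 spans those weeks; what is absent is an observed utility within them. Interpolation is itself an assumption here, since the article fixes no QALY method. The error can be nil or reverse in sign, and zero QALYs requires complete loss of benefit by week 20.

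It is also fair to object that making week 16 the main comparison would change a secondary time point after randomisation has begun in a prospectively registered trial. That stands, and it is why week 16 should be added beside week 20 and not put in its place. What remains is that the stated aim on quality of life and the economic analysis both lack a reading at the point where treatment ends.

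**Conclusion.** The point holds in limited form. EHP-30, SF-12 and EQ-5D have no on-treatment or end-of-treatment reading; this follows from the schedule and needs no assumption beyond taking one month of recall as four weeks. The planned comparison estimates a post-treatment effect and can miss a benefit that fades on stopping.

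The effect on QALYs cannot be sized from the documents. With linear rise to week 16, linear interpolation and no more benefit at week 20 than at week 16, two readings recover between 0% and 80% of what three would show. With full benefit by week 8, they recover between 0% and 57% of the true gain. If benefit builds linearly to week 20, nothing is lost. The finding concerns secondary and economic outcomes; the primary pain outcome is measured on treatment and is not affected. The change should be made, since it is cheap and lets the trial answer its own question on quality of life.

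**What to change.** - Add EHP-30 and EQ-5D (online) at the existing week-16 contact, where the FSS is already taken, and the SF-12 too if the cost of another paper round is acceptable. Do this by a dated, registered amendment made while blinded.
- Report week 16 as the end-of-treatment quality-of-life comparison alongside the planned week-20 comparison. Keep the latter and label it a post-treatment effect.
- Compute QALYs as area under the curve from weeks 4, 16 and 20. Add sensitivity analyses for the course of utility on treatment (slow and fast onset) and for women already past week 16 who lack that reading.
- If recruitment is too far advanced to collect the reading, still label the quality-of-life results as post-treatment effects and run the QALY sensitivity analyses.

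The cost is an amendment, one more set of forms per woman at a contact that already takes place, and missing week-16 values for those past that point. At manuscript submission 24 of a planned 90 had been randomised, so at that time most women could still have supplied it. A week-16 reading would also give a post-baseline value for women lost during the last four weeks; the article predicts 20% dropout but does not say when it falls.

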#### Fatigue severity scale (FSS)

The fatigue severity scale is a nine-item, seven-point questionnaire used to determine the impact of fatigue when performing daily activities [18]. This will be used as an adjunct to the numerical ratings given for daily fatigue, to provide a measure of the real-world impact of fatigue. This tool uses a seven-day recall. This will be administered online at baseline and at the end of the intervention.

### Participant safety

The product has been listed as a listed medicine on the Australian Register of Therapeutic Goods (ARTG) (AUST L 197899). As the investigational product (Gynoclear™) is a low-risk product already approved by the Australian Therapeutic Goods Administration and available for purchase through health care practitioners. No adverse effects from oral consumption at the dosages outlined have been reported to the Australian Therapeutic Goods Administration. A formal data monitoring committee will not be established in Australia, however, the nominated medical representatives for the study, [name], is a registered General Practitioner in Australia and will review safety on all adverse events.

Methods for adverse event recording and reporting include at all study visits beginning at the week 2 phone call and up until trial completion. Participants are also encouraged to report any safety concerns as soon as they become aware of it and have been provided with a written information sheet detailing the research team’s contact details (i.e. Clinical Trial Coordinator and Chief Investigator) for referral to the [name].

Safety markers in the blood will be tested at baseline and at trial exit. Participants will be asked to go to their local Laverty Pathology (or sister companies depending on region) collection centre. These safety tests will consist of the following markers in the blood: liver enzymes, bilirubin and albumin (liver function tests (LFTs)), urea and electrolytes (U&E) and red and white blood cells (full blood count). Electronic copies of blood test results will be sent to the medical representative of this study ([name]) for review when there are indications that blood markers are outside normal reference ranges.

### Compliance

At each contact point (2-week phone call and midpoint call) compliance is checked verbally. At the midpoint, participants will be asked to return their three most empty trial product containers. These will be checked for compliance (75% or greater adhereance to the daily dose will be considered compliant) before the remaining trial product is dispensed. A similar procedure will occur at the end of treatment where participants are asked to return all remaining trial product.

### Withdrawal

Participants who withdraw will have the reason for withdrawal (e.g adverse events, lack of efficacy) documented.

### Concomitant medication

All participants are advised to continue taking their medications as per their doctors’ advice. Changes in concomitant medication are monitored via the study diaries.

### Analysis plan

All data is captured via Castor EDC digitally, there are no paper instruments used in this trial. Data will be exported from Castor EDC into SPSS v24 (or greater). Prior to analysis, data will be cleaned by examining frequencies, means, medians, and ranges to identify logical errors. Instruments will be coded according to their respective scoring instructions. Unless specified by the instrument, missing items will be imputed based on averaging values within the instrument for a given individual, if no more than 15% of items are missing. Otherwise, that instrument will be set to missing for the individual.

Baseline demographics will be reported using descriptive statistics. Daily pain scores (as measured by the EPDD) will be converted into a single pain score at five time points, baseline, month 1, month 2, trial exit/end of intervention and follow-up. This single pain score will be achieved by taking the mean of the daily pain scores for the previous 4 weeks. Both a per-protocol and intention to treat analysis will be undertaken for the primary outcome of changes in pain scores. The same process of generating a single score will be used for the following outcomes: pain interference with activities of daily living (0–10), use of analgesics (number of days per month needing additional medication), severity of fatigue (0–10) and severity of dyspareunia (0–10). All scores will be analysed using repeated measures at baseline, month 1, month 2, trial exit and follow-up via a longitudinal linear mixed model analysis of variance with time and group as fixed effects and subject as a random effect.

Secondary outcomes of changes in EHP-30 scores, SF-12 scores and EQ-5D scores will be analysed using analysis of variance between baseline and one-month follow-up. FSS scores will be analysed using paired analysis of variance between baseline and the end of the intervention. Baseline values with be used as covariates in the analysis.

A cost-effectiveness (cost-utility) analysis will be conducted alongside the trial following international best practice [19]. This will assess the difference between trial arms in (i) costs—the cost of introducing modified GZFLW and the use of analgesic medications, measured using Medicare Benefits Scheme/Pharmaceutical Benefits Scheme, and (ii) effects—the difference in an economic measure of health-related quality of life, called the EQ-5D, which is used in estimating quality-adjusted life years. A cost-effectiveness analysis, combining i and ii, will then be conducted including subgroup analysis. Further, statistical uncertainty will be explored in a Probabilistic Sensitivity Analysis, health-related quality of life will be cross-validated using the SF12, and a Value of Information analysis will assess whether further research is required before making recommendations to mainstream modified GZFLW in routine practice.

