### Recruitment and selection

Recruitment for this study is primarily via our partners Endometriosis Australia social media presence as well as paid Facebook advertising. All advertisements will advise participants of the trial and refer them to the Research Institute webpage. A link to a pre-screening survey will be available on the webpage to allow participants to self-screen against the inclusion and exclusion criteria of the study. All potentially eligible participants, based on their responses from the survey, will be instructed to schedule a call with the clinical trial officer or another member of the research team for follow-up procedures.

Potential participants will be required, after giving consent, to fill in a previously validated endometriosis daily pain diary (EPDD v3) [12] via an online secure electronic case report form hosted on Castor EDC. This diary will be filled in for 4 weeks and will fulfil two purposes:
Ensure that the participant meets the minimum pain requirements to enter the study andIf the participant is included in the study, this becomes the baseline/pre-treatment data for future analysis.

If eligible based on pain diary scores (averaged across 4 weeks), participants will be required to provide a copy of their most recent laparoscopy report and/or the gynaecologists report/letter that confirms visualisation of endometriosis. This must be within the previous 5 years of their entry into the trial. Upon receipt of the completed EPDD and the proof of surgical confirmation, participants will be included in the study.

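### As written, the primary mixed model has no term for change in pain: its group effect averages in a pre-treatment and an off-treatment month and recovers 60–80% of a constant treatment effect

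*Protocol article*

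**What the plan says.** Table 3 of the protocol article states that efficacy will be judged "by change in endometriosis-related pain based on the Endometriosis pain daily diary v3 (EPDD) scores". The Analysis plan turns the daily diary into five scores: "This single pain score will be achieved by taking the mean of the daily pain scores for the previous 4 weeks". On the model it says: "All scores will be analysed using repeated measures at baseline, month 1, month 2, trial exit and follow-up", by means of a "longitudinal linear mixed model analysis of variance with time and group as fixed effects and subject as a random effect".

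Two other sections fix the treatment status of each window. Outcome measures and data capture gives "4 weeks prior to trial entry to perform baseline pain screening diary, 12 weeks of active treatment and 4 weeks of follow-up". Recruitment and selection says of the screening diary that "this becomes the baseline/pre-treatment data for future analysis". So one window lies wholly before treatment, three lie on treatment, and one lies wholly after it.

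The next paragraph of the Analysis plan covers EHP-30, SF-12, EQ-5D and FSS. It ends with "Baseline values with be used as covariates in the analysis".

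**The concern.** A mixed model with baseline among the responses estimates a treatment effect on change only through the group-by-time term. The article lists the fixed effects, and that term is not among them. With main effects alone, the model assumes the same difference between arms in every window, including the one before randomisation, and reports a single average difference in level.

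That average differs from the stated primary outcome in three ways:

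- It counts a window in which the true difference is zero.
- It counts a window in which nobody takes capsules.
- It carries any chance baseline imbalance into the estimate instead of adjusting for it.

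An analyst who follows the sentence literally would report too small an effect for the primary outcome of a small trial, and would have no between-group estimate at a named on-treatment time.

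**Working it through.** **Inputs from the article.** SD 2.2; d = 0.5, so D = 0.5 × 2.2 = 1.1 points; 45 per arm with 20% dropout, so 45 × 0.8 = 36 per arm; alpha 0.05, taken as two-sided.

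**Assumptions, because the article gives no figure.** Within-woman correlation ρ = 0.4 to 0.7, equal between all pairs of windows (the structure that a random subject effect implies); share f of the effect still present at follow-up, from 0 to 1; complete, balanced data; normal approximation.

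**The plan's own figure.** The stated 74 participants do not follow from d = 0.5 with 80% power: 2 × (1.96 + 0.842)² / 0.5² = 62.8, so 63 per arm, 126 in all. That is a separate matter and nothing below depends on it. The article also calls the target a 20% difference on a 0–10 scale, which could mean 2.0 points. The fractions below hold for any D.

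**1. What the group term estimates.** With balanced data it is the unweighted mean of the five window differences, (0 + D + D + D + fD) / 5.

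| Persistence f | Share of D | D = 1.1 | D = 2.0 |
|---|---|---|---|
| 0 | 0.60 | 0.66 | 1.2 |
| 0.5 | 0.70 | 0.77 | 1.4 |
| 1 | 0.80 | 0.88 | 1.6 |

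Mixed models fitted to simulated trials (150 per scenario, 37 per arm, ρ = 0.5, true effect 1.1) agree. The group term averaged 0.68 for f = 0 and 0.89 for f = 1. In a model with the interaction, the exit-by-group term averaged 1.14 and 1.06.

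**2. Power, 36 per arm, D = 1.1.**

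- Group term: SE = √[2 × 2.2² × (1 + 4ρ) / 5 / 36]. At ρ = 0.6 this is 0.428.
- Baseline-adjusted contrast at end of intervention: SE = √[2 × 2.2² × (1 − ρ²) / 36]. At ρ = 0.6 this is 0.415.
- Power = Φ(estimate / SE − 1.96).

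| ρ | Group term, f = 0 | Group term, f = 1 | Adjusted contrast at exit |
|---|---|---|---|
| 0.4 | 42% | 65% | 64% |
| 0.5 | 38% | 59% | 69% |
| 0.6 | 34% | 54% | 76% |
| 0.7 | 31% | 49% | 84% |

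At ρ = 0.3, below the assumed range, the figures are 48%, 73% and 60%.

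**3. Where the gain from averaging comes from.** A baseline-adjusted mean of the three on-treatment months has SE = √{2 × 2.2² × [(1 + 2ρ)/3 − ρ²] / 36}. For a constant effect of 1.1 its power is at least 89% for ρ from 0.3 to 0.7. So where the group term does well, it does so because it averages post-baseline months, not because baseline is in the average.

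**The case against.** The strongest reply is that the article never says these are the only terms. It is one sentence in a condensed paper, it may simply name the two factors, and the same paragraph speaks of changes in pain scores, which suits an intended interaction test. A full protocol exists and may contain that term. This limits what can be said about intent: a reader might infer that the trial team will in fact fit a model that cannot estimate change, and the article does not establish that. It does not rescue the sentence, which lists the fixed effects and omits the one that bears on the primary outcome. That is a model stated wrongly rather than a detail left to another document.

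Three stronger readings are tempting and are not supported.

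- *The primary test necessarily loses much of its power.* It does not. At ρ = 0.4 with full persistence the group term has 65% power against 64% for the adjusted exit contrast, and at ρ = 0.3 it is ahead. Dilution of the estimate follows from the model as written; loss of power depends on two quantities the article does not give.
- *Baseline is both response and covariate in the primary model.* The covariate sentence closes the paragraph on the secondary questionnaires and is not clearly tied to the mixed model. If it did apply, the simulated group term stayed diluted (0.67 and 0.86), although rejection rates rose to 78% and 90% at ρ = 0.5, so the remaining fault would be the size of the estimate rather than power.
- *End of intervention is the only proper target.* The mean over the on-treatment months is equally legitimate. The article does not decide between them.

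**Conclusion.** Wrong as written. The stated model contains no parameter for a between-group difference in change, and its group term recovers 60% to 80% of a constant on-treatment effect: 0.66 to 0.88 points where the truth is 1.1. The range assumes a constant effect over the three treated windows, balanced data and between none and all of the effect persisting off treatment. Even with full persistence one fifth is lost, because the baseline window contributes zero.

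The consequence for power is conditional. Under the assumed correlations of 0.4 to 0.7 it runs from a large loss (31% against 84% at ρ = 0.7 with no persistence) to none (65% against 64% at ρ = 0.4 with full persistence).

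**What to change.** Restate the primary model with group, time and group-by-time as fixed effects and subject as random. Let baseline pain enter in one way only: as a covariate with the post-baseline scores as responses, or as a response with its mean constrained equal across arms. Pre-specify one on-treatment between-group contrast with its 95% CI as the primary estimate, either at end of intervention or as the mean of the on-treatment months. Report the follow-up month separately, as persistence after treatment. Say explicitly whether the sentence on baseline covariates applies to the mixed model.

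The cost is analysis wording only, with no new data. The article reports recruitment as ongoing and analysts as blinded, so the change could be settled before unblinding.
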